### Intervention group

The intervention involve collaboration between a nurse with geriatric competence at the emergency ward, the hospital wards and a multi-professional team for care of the elderly with a case manager in the municipality. The multi-professional team includes professionals with university degrees in nursing (the case manager), social work, occupational therapy and physiotherapy. The aim is to create a continuum of care from the emergency department, through the hospital ward to the elderly person's own home. In addition, there is support for relatives, initiated as early as at the hospital.

At the emergency ward, the nurse with geriatric competence made an assessment of the elderly patient's needs of rehabilitation, nursing, geriatric and social care. This assessment was transferred to the ward and to the case manager in the municipality. The case manager is responsible for contacting the ward and the patient in order to initiate discharge planning. Discharge planning is done in collaboration between the case manager, a social worker, the patient, and the nurse and physician in charge at the ward. Patient care planning is done in the elderly person's home within a couple of days after discharge. Patients discharged directly from the emergency ward were offered patient care planning by the case manager and the team. The multi-professional team is responsible for the patient care planning, which is done by involving the patient throughout the intervention. The care planning is based on a comprehensive geriatric assessment done by the team, followed up after one week by the case manager, and then at least every month. The elderly person is included in the intervention for at least one year.

The case manager contacts the relatives/informal caregivers, if approved by the elderly person, to give information/involve them in the planning and to offer them support and advice. This is initiated as soon as possible, often as early as when the elderly person is in the hospital.

### Control group

The control group receives conventional care and follow up. Access to a case manager or multi-professional team is not part of the present organization of municipal care for elderly persons living in Mölndal. When needed, the patient care planning is done at the hospital by a team from the community consisting of different professional groups (social worker, nurse and occupational therapist or physiotherapist) responsible for all care planning at the hospital. After discharge, another team from municipality elderly care - known as the district team - is responsible for the follow-up of the care planning. If the patient is discharged from the emergency department directly to their home, there is no routine for information transfer from the hospital to the municipality. In addition to conventional care, there are also assessments at the research follow ups for the control group - the same as for the intervention group, see under procedures below. If unmet needs are revealed at these research follow-ups, the elderly person will get advice on where and how to seek help.

### Procedure of the intervention study

The participants were recruited at the emergency wards. The nurse with geriatric competence screened most of the patients during her work shift (daytime, weekdays, approximately 3-4 days per week) to see if they fulfilled the inclusion criteria. If so, the nurse informed them about the study both verbally and in writing. The information included a description of the study, how it would be conducted and what was expected of people who agreed to participate. There were opportunities to ask questions if anything was unclear. It was stressed, both in the verbal and the written information that participation was voluntarily. Of all those invited to participate, 17 were invited by letter, as they had been discharged before the nurse was able to ask them. People who accepted to participate in the study were randomised to intervention or control by using a system of sealed opaque envelopes. All participants signed a written consent form. The study started with a pilot study to test intervention, inclusion/exclusion criteria and logistics. The pilot study comprised the first ten included participants.

A baseline interview and assessment were done within a week of discharge. In some cases it was not possible to do the baseline interview so soon, mostly because the frail elderly person not having enough strength. Follow-up data are collected at 3, 6 and 12 months, see table 1 for description of the objectives, outcome measures and follow ups of the study. On the follow ups, there was also sometimes a delay, owing to the frail elderly person's lack of strength or readmission to hospital. The baseline interviews for the intervention group were done by the multi-professional team as part of their comprehensive geriatric assessment. The baseline interview for the control group and all follow ups for both groups were done by research assistants, who were occupational therapists, nurses or social scientists. The interviews were performed in the participants' home. All interviewers were well trained in interviewing, assessing and observing, according to the guidelines for the different outcome measurements. It was not possible to keep the interviewer blinded to group assignment when doing the follow ups. The reasons for this are threefold: 1) in most cases the participant revealed the assignment unintentionally; 2) some elderly people were not aware that the case manager was part of the intervention and thus did not answer the questions about their experience of receiving the intervention unless the research assistant knew that they were assigned to the intervention; and 3) we assumed there would be less attrition if the elderly person could meet the same research assistant for most of the follow ups.

**Table 1 T1:** Outcome measures and follow ups

Primary Outcome	Measurement	T0 baseline	T1 3 months	T2 6 months	T3 1 year
Health care consumption	Register data				
Satisfaction with health and social care	Questionnaire	X	X	X	X
Functional ability	The Berg Balance Scale	X	X	X	X
	Gait speed four-meter walking test	X	X	X	X
	Grip strength: North Coast dynamometer	X	X	X	X

**Secondary Outcome**	**Measurement**				

Fatigue	Tiredness scale	X	X	X	X
Physical activity	Questionnaire	X	X	X	X
	Physical and domestic activity scale	X	X	X	X
Activities of daily living	The ADL staircase	X	X	X	X
Weight loss	The Göteborg Quality of Life Instrument	X	X	X	X
Cognition	Mini mental State Exam (MMSE)	X		X	X
Visual impairment	KM visual acuity chart	X		X	X
Depression	GDS 20	X	X	X	X
Health-related quality of life	EQ5D	X	X	X	X
Life satisfaction	Fugl-Meyer - LiSat	X	X	X	X
Participation/leisure activities	Questionnaire	X	X	X	X
Social support	Questionnaire	X	X	X	X
Falls	Questionnaire	X	X	X	X
Fear of falls	FES-I	X	X	X	X
Decisional autonomy	Impact on Participation and Autonomy Questionnaire	X	X	X	X
Self-rated health	SF 36 (one question)	X	X	X	X
Illness	CIRS-G	X		X	X
Symptoms	The Göteborg Quality of Life Instrument	X	X	X	X
Mortality	Register data				

Meetings are held regularly with all personal in the intervention from one month before starting the inclusion process and throughout the entire intervention period (including the pilot study). In addition, the project leaders for the research and the different care levels, i.e. emergency care, municipal care and primary care, meet regularly during the intervention period.

## Research questions and outcome measures

There are two overarching research questions:

1) Can an intervention for frail elderly people at risk of high care consumption

• decrease health care utilization?

• maintain/increase functional abilities, activities of daily living, health related quality of life and life satisfaction?

• increase satisfaction with rehabilitation, health and social care for the frail elderly and their relatives?

• be cost-effective?

2) Which obstructing and facilitating components can be identified when implementing the intervention

• on the operative level, concerning the actions of the professionals involved?

• on the operative and management level regarding cognition, expectations, commitment and perceived resources?

• on the organizational level, concerning content, process and environment?

### Primary outcome measures

Health care consumption, functional abilities and satisfaction with health and social care.

### Secondary outcome measures

Fatigue, physical activity, activities of daily living, cognition, visual impairment, quality of life, life satisfaction, accessibility, social support, falls, fear of falls, decisional autonomy, morbidity and mortality.

### Measurements of frailty indicators

We use the same definitions and measurements of frailty as the study "Elderly persons in the risk zone" [28] which also is part of the research programme "Support for frail elderly persons - from prevention to palliation". A more detailed description of the frailty indicators is given in the study protocol for "Elderly persons in the risk zone" [28].

The following definitions/cut-off levels of frailty are used:

**Weakness: **Reduced grip strength was considered to be below 13 kg for women and 21 kg for men for the right hand, and below 10 kg for women and 18 kg for men for the left hand, using a North Coast dynamometer [29].

**Fatigue**: Answering Yes to the question "Have you suffered any general fatigue/tiredness over the last three months? (part of "The Göteborg quality of life instrument" [30]).

**Weight loss**: Answering Yes to the question "Have you suffered any weight loss over the last three months? (part of "The Göteborg quality of life instrument" [30]).

**Reduces physical activity**: Taking outdoor walks 1-2 walks/week or less.

**Impaired balance**: Having a value of 47 or less on the Berg Balance Scale [31-33].

**Reduced gait speed**: Walking four metres with a gait speed of 0.6 metres/second or slower [34].

**Visual impairment**: Having a visual acuity of 0.5 or less using the KM chart [35].

**Impaired cognition**: Scoring below 25 on the Mini Mental State Examination (MMSE) [36].

### Statistical analysis and power calculation

A power calculation was done before the start of the study. The calculation was based on the expected relative change over time in functional abilities, i.e. we assumed that the intervention group would change slightly or not at all in their functional status and that the control group would deteriorate by 20% in relation to the intervention group (this assumption was based on clinical experience). Power calculations ensured that we would be able to reveal a difference of at least 20% between the groups, if the hypothesis was true. To be able to detect a difference of at least 20% with a two-sided test and with at significance level of alpha = 0.05 and 80% power we needed at least 95 people in each group. Thus a total of approximately 200 people was planned to be included.

An interim analysis was made to evaluate whether or not the assumed difference evaluation was relevant. This was done with knowledge of more specific prevalence rates of functional abilities which, since the study began, have been gained from the study "Elderly persons in the risk zone" [28]. This knowledge enabled us to make a more detailed power calculation. The prevalence rates were for less frail elderly persons than those in our study. Thus we assumed lower functional status and higher standard deviance. This power calculation was based on the balance scale (one of the primary outcome variables, range 0-56), with an assumed mean for the intervention group of 32 and for the control group of 28 (15% difference), and a standard deviation of 8 in both groups. To be able to detect a difference between the intervention and control groups with a two-sided test and with a significance level of alpha = 0.05 and 80% power we would need at least 65 people in each group.

The analysis will be made on the basis of the intention-to-treat principle, meaning that participants will be analysed on the basis of the group to which they were initially randomised [37]. Both descriptive and analytic statistics will be used to compare the two groups as well as for analyses of changes over time. Non-parametric statistics will be used when ordinal data are analysed. Otherwise, parametric statistics will be used.

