**Figure 1 F1:**
[figure not shown]
**Flow chart of enrolment, allocation and baseline**.

The median age of the participants was 83 in both groups, with the age range of 66-92 in the control group and 70-96 in the intervention group. Visual impairment was more common in the control group. Otherwise there were no statistically significant differences between the groups in terms of baseline characteristics concerning demographic and frailty indicators, see tables 3 and 4. The non-participants had a median age of 78 (range 69-94), and 61% were women.

**Table 3 T3:** Baseline characteristics of study participants

Characteristics	Control group n = 76 %	Intervention n = 85 %	p-value
Female	55.3	55.3	1.00
Living alone	60.5	56.5	0.63
Academic education	15.8	12.2	0.51
Self-rated health (excellent/very good/good)	28.0	40.7	0.10

**Table 4 T4:** Frailty indicators of study participants

Frailty indicators	Control group n = 76 %	Intervention n = 85 %	p-value
Weakness	23.6	21.3	0.85
Fatigue	69.7	72.8	0.73
Physical activity	51.3	46.4	0.63
Weight loss	40.8	35.8	0.62
Gait speed	57.3	51.2	0.52
Poor balance	60.0	54.8	0.52
Visual impairment	85.5	70.6	0.02
Impaired cognition	3.9	9.9	0.21

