## Discussion

The study "Continuum of care for frail elderly people" was designed to evaluate whether or not a multi-professional and multidimensional intervention targeting frail elderly persons can decrease health care utilization, maintain functional abilities and increase satisfaction with health and social care. One of the major strengths of this study is that the implementation of the intervention programme is followed and analysed throughout the study. This enables us to generate knowledge on the process of implementing complex intervention in health and social care settings, both in term of how the intervention is perceived and translated into practical clinical work and to see what is in the "black box", i.e. to explore how and why different parts of the intervention were/were not implemented. Another major strength is that it has both an explorative and experimental design, facilitating multi-facetted knowledge production. In addition, it is a randomised controlled study, which is very important for the possibility of drawing valid conclusions from the results.

We were not able to include as many frail elderly people as was at first calculated. Still, the 181 included are sufficient enough according to the more detailed interim power calculation, and should be enough even the inevitable attrition in the follow ups. The non-participation rate, 46.8%, is in line with what can be expected for this very frail elderly group of patients, especially as they had to decide whether or not to participate when at the emergency ward with acute symptoms. The median age of the non-participants was somewhat lower than the participants, but the age range was about the same. The most common reasons for not participating were that the study seemed too demanding. There were also a number of persons who were too healthy to see any reason to participate. Thus, there are indications of the non-participants being both healthier and less healthy than the participants. Therefore, the participants can be seen as a fairly representative sample of the frail elderly population.

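### The revised power calculation pairs Berg means of 32 and 28 with an SD of 8, which the trial's own baseline balance data exclude, so the claim that the sample is sufficient is unsupported

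*Protocol article*

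**What the plan says.** The Statistical analysis and power calculation section describes two calculations.

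- The first, made before the study, led to 95 per group and about 200 in total. It names no scale, mean or SD. Of the expected course it says "we assumed that the intervention group would change slightly or not at all in their functional status".
- The second, made at an interim point, uses the Berg Balance Scale: "This power calculation was based on the balance scale (one of the primary outcome variables, range 0-56". Its inputs are extrapolated from a less frail cohort in a sister study: "Thus we assumed lower functional status and higher standard deviance". It takes an "assumed mean for the intervention group of 32 and for the control group of 28 (15% difference), and a standard deviation of 8" and concludes that "with a two-sided test and with a significance level of alpha = 0.05 and 80% power we would need at least 65 people in each group".

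Two other places bear on these inputs. The Measurements of frailty indicators section defines impaired balance as "Having a value of 47 or less on the Berg Balance Scale". Table 4, under Baseline characteristics, gives the share meeting that definition in the control group, the share in the intervention group, and the p-value: "Poor balance 60.0 54.8 0.52".

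The Discussion concedes that recruitment fell short of the first target. It then states that "the 181 included are sufficient enough according to the more detailed interim power calculation", and that the number should withstand attrition. No attrition figure is given, and no observed Berg mean or SD appears anywhere in the article.

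**The concern.** If 60.0% and 54.8% scored 47 or less, then 40.0% of controls and 45.2% of the intervention group scored between 48 and 56. A group averaging 32 with an SD of 8 would have to place that share two or more SDs above its mean, and a group averaging 28 would have to place it 2.5 SDs above. That cannot happen.

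This matters because the second calculation is the only support offered for calling the achieved sample adequate, and functional ability is one of the primary outcomes. If the true SD is well above 8, the trial has much less than 80% power for a 4-point difference, and a null result on balance could be misread as evidence of no effect. If instead the true means are well above 32, a 4-point difference is a different target on a scale that ends at 56. It then needs its own justification.

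**Working it through.** **Inputs.** Means 32 and 28 (difference 4), SD 8, two-sided alpha 0.05, power 80%, 65 per group: Statistical analysis and power calculation. Cut-off 47 or less: Measurements of frailty indicators. Baseline shares: Table 4. Arm sizes 76 and 85: Tables 3 and 4. The percentages fit 45/75 and 46/84 at or below 47, hence 30/75 and 38/84 at 48 or more; these counts are inferred.

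**1. Reproduce the stated figure.**
n per group = 2 × (1.960 + 0.842)² × (SD/difference)² = 2 × 7.85 × (8/4)² = 62.8, so 63. By the t-test it is 64. Power at 65 per group is 81.3% (80.8% by t-test). The stated 65 follows from its inputs.

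**2. Test the inputs against Table 4.** The one-sided Chebyshev (Cantelli) inequality holds for any distribution:
P(X ≥ 48) ≤ SD² / (SD² + (48 − mean)²).

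| Arm | Assumed mean, SD | Maximum share at 48+ | Normal shape | Baseline share | 95% lower limit |
|---|---|---|---|---|---|
| Intervention | 32, 8 | 64/(64 + 256) = 20.0% | 2.6% | 45.2% | 34.3% |
| Control | 28, 8 | 64/(64 + 400) = 13.8% | 0.7% | 40.0% | 28.9% |

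Even the lower confidence limits exceed the maxima, so sampling error does not explain the gap.

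**3. Could 32 and 28 hold at follow-up?** The share at 48 or more would have to fall by at least 45.2 − 20.0 = 25.2 percentage points in the intervention group and 40.0 − 13.8 = 26.2 in the control group.

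**4. Which input gives way?** With share p at 48 or more:

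- *Keep the means.* Minimum SD = (48 − mean) × √(p/(1 − p)). Intervention: 16 × √(0.452/0.548) = 14.5. Control: 20 × √(0.400/0.600) = 16.3.
- *Keep the SD at 8.* Minimum mean = 48 − 8 × √((1 − p)/p). Intervention: 39.2. Control: 38.2. Four points is then 4/39.2 = 10.2% or 4/38.2 = 10.5% of the mean, and less if the mean is higher.

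**5. Power for a 4-point difference**, Φ(4/(SD × √(2/n)) − 1.96), with the two arm sizes entered separately in the last column:

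| SD | 65 per group | 76 and 85, no attrition |
|---|---|---|
| 8 | 81% | 89% |
| 10 | 63% | 72% |
| 12 | 48% | 56% |
| 14.5 | 35% | 42% |

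Reaching 65 means losing 11 of 76 controls (14%) and 20 of 85 in the intervention group (24%).

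**6. The relative difference.** 4/32 = 12.5% and 4/28 = 14.3%; neither is 15%. The percentage does not enter the sample-size formula.

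**The case against.** Much of the case on the other side stands.

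- *A reader might infer that the 80% power is false.* The documents do not show that. Power depends on the difference and the SD, not on the level of the means. Table 4 excludes the pair, not the SD of 8 alone. With means of about 38 to 39 or higher, 65 per group still gives about 81% for 4 points.
- *The low-power branch is the less natural one.* For the intervention mean to be 32 with 45.2% at 48 or more, the remaining 54.8% would have to average at most (32 − 0.452 × 48)/0.548 = 18.8. Nothing in the article suggests such a split. An assumed mean that was simply too low is easier to believe. The 35% is therefore one end of a range, not the expected power.
- *Table 4 is baseline, while 32 and 28 presumably describe follow-up.* This is correct, so follow-up values of 32 and 28 are not strictly impossible. But they would need the falls shown in step 3, against a stated expectation of little or no change in the intervention group. That expectation belongs to the first calculation; no other course is given for the second, and the hypothesis is that function is maintained.
- *A reader might infer that recruitment was stopped on the strength of this calculation.* The Discussion does not say so. It reports a shortfall and then cites the calculation as reassurance.
- *A reader might see a contradiction in the requirement falling from 95 to 65 while a higher SD was assumed.* There is none. The first calculation names no scale or SD, and the higher SD is relative to the less frail cohort.

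**Conclusion.** The point holds in a limited form. The revised calculation is arithmetically correct, but its mean and SD cannot together describe the enrolled participants at baseline: 45.2% and 40.0% at 48 or more, against maxima of 20.0% and 13.8%. That exclusion needs no distributional assumption. Carrying it to follow-up rests on the article's own expectation of little change in the intervention group.

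The stated 80% power and the assurance of sufficiency after attrition are thus unsupported rather than refuted. At 65 per group, power for 4 points lies anywhere from about 81% (SD 8, means of about 38 to 39 or more) to about 35% (SD 14.5, the minimum if the intervention mean is 32). In the favourable branch the open question moves to the target: about 10% of the mean or less, on a scale capped at 56, where a 4-point separation may be harder to reach. The documents give no observed Berg mean or SD with which to choose between the branches. The loose 15% is a minor slip.

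**What to change.** 1. Compute the Berg mean and SD from the baseline scores already held (about 159, on the inferred counts), pooled across arms so that no treatment comparison is made.
2. With that SD, restate the power and the detectable difference at the numbers expected after attrition, and state the attrition assumed. Start from the correct total: the Discussion gives 181, while Study population and the baseline tables give 161 (76 + 85).
3. Justify the target difference in points, given the observed mean and the ceiling of 56.
4. Qualify or withdraw the sufficiency statement in the Discussion if the restated figures do not support it.
5. Replace the 15% with 12.5% (of 32) or 14.3% (of 28), naming the base, or with the new figure.

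The cost is one recalculation and a few changed sentences. It needs no extra enrolment and no change to conduct or analysis. The stated power or detectable difference may become less favourable. One-year follow-up was planned to run to July 2011, so the restatement could be made before the final comparison and would fix in advance what a null result on balance can be taken to mean.
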